#### Secondary outcomes

A structured interview will be communicated through video conferencing sessions via VSee video connection to evaluate secondary outcomes that may act as independent variables or confounders. The structured interview includes domains (sociodemographic, pregnancy-related characteristics, current medical problems in pregnancy, corona status, medications, previous maternal and neonatal complications, chronic diseases, mental history, behavioral factors, and possible psychosocial stresses).

### Statistical methods {14}

The required sample size was calculated using the sample size calculation OpenEpi® software version 3.01 available online [24]. In testing the null hypothesis at a 95% level of confidence interval (CI), the error rate of 5% with power = 80%. We used the following formula for sample size calculation:
$$ \mathrm{n}1=\left(\mathrm{Z}\upalpha /2+\mathrm{Z}\upbeta \right)2\ast \left(\mathrm{p}1\left(1-\mathrm{p}1\right)+\mathrm{p}2\left(1-\mathrm{p}2\right)\right)/\mathrm{r}\left(\mathrm{p}1-\mathrm{p}2\right)2 $$

and

n2 = r*n1

where:

n1 = number of exposed (intervention group)

n2 = number of unexposed (control group)

Zα/2 = standard normal deviate for the two-tailed test based on alpha level (relates to the confidence interval level) [alpha = 0.05]

Zβ = standard normal deviate for the one-tailed test based on beta-level (relates to the power level) [beta = 0.2]

r = ratio of unexposed to exposed = 1

p1 = proportion of exposed with the outcome: incidence in intervention group: 34% (we used results from two studies that showed and an improvement between 34 and 69% after delivering the interventions to pregnant women) [18, 25].

p2 = proportion of unexposed with the outcome: incidence in the control group: 70% (since no similar studies have been conducted locally; hence, the estimate p1 was set to 70%).

The sample size needed for each group would be 29 pregnant women, and the total would be 58 participants.

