## Introduction

### Background and rationale{6a}

The infectious outbreak of the novel coronavirus was first identified in Wuhan City, China, and reported to the World Health Organization (WHO) on December 31, 2019. COVID-19 caused by severe acute respiratory syndrome coronavirus 2 (SARS-CoV-2) has been widely publicized as “killer pneumonia” transmitted via droplets and fomites during close unprotected contact between an infector and infected with no precise treatment [1]. The life-threatening aspect of COVID-19 was vividly described by the media, constantly alarming people of the dangers of this disease. In addition to the actual physical health danger posed by the virus, the pandemic has also impacted mental health [2].

Perinatal depression and anxiety are increasingly recognized as crucial public health issue [3]. Emerging infectious outbreak decreases social support and fuels perinatal mental health disorders. For instance, a previous infectious outbreak revealed that pregnant women tend to overestimate the risk of contracting respiratory illness and report higher anxiety levels [4]. Recent data show a higher prevalence of psychological distress (anxiety and depression) in pregnancy during the COVID-19 pandemic across several countries [5–7].

During the pandemic, the burden of perinatal health problems reported in Qatar was higher than before the pandemic; perinatal depression increased by 10% (24% vs. 34.4%), and perinatal anxiety increased by 22.8% (16.4% vs. 39.2%). These studies reported the prevalence based on screening tools and utilized similar conceptual definitions in distinguishing depressed and anxious pregnant women from those without outcome [8–10]. The alarming rise in perinatal mental health distress may negatively affect the expecting mothers and their offspring leading to an increase in the infants’ risk of pre-term delivery and neurodevelopmental disorders [11]. Crucial interventions are needed to address perinatal psychological distress among Qatar’s maternal population during the pandemic.

Most guidelines recommend psychological or behavioral treatments as first-line therapy for pregnant women with mild to moderate depression [12], considering it an essential strategy for mitigating postnatal depression and preventing behavioral and developmental problems in upcoming children [13, 14], supported by the United States Preventive Services Task Force (USPSTF) recommendation [15].

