## Discussion

To our knowledge, this study is the first research to examine the effectiveness of maternal low-intensity psychosocial telemental interventions in preventing perinatal distress in response to COVID-19 in Qatar.

Cumulative evidence showed that individual psychosocial interventions were more effective than group interventions in preventing and treating perinatal depression. Specifically, face-to-face CBT revealed a protective effect (OR 0.64; 95% CI [0.53–0.75]) and a preventive effect (OR 0.39; 95% CI [0.17–0.60], p 0.001) [26]. Therefore, the regional body of research agreed on the beneficial effects of face-to-face psychosocial interventions. However, there is a lack of studies concerning the effect size of the telemental health approach on perinatal mental health an identified gap to be tested.

The results from this study will show whether maternal low-intensity psychosocial telemental interventions is preventive or not and whether it is recommended to be part of the antenatal package delivered to pregnant women during the COVID-19 pandemic.

One of this study’s strengths is at the level of methodology; applying randomization as a strategy could deal with bias and determine the effectiveness of an intervention in a reliable approach [27]. The prospective nature of the design ensures the temporality between variables and preserves the causation effect. Utilizing a probability sampling technique preserves the external validity of the study. Furthermore, several strategies were employed to decrease the measurement bias, which included extensive training, blinding, and selecting reliable screening tools for assessment. Moreover, it will provide valuable insights into the acceptability of telemental interventions among pregnant women in Qatar, but it is not without limitations. The sample size is not big enough, limiting the generalization of results, and loss of follow-up could be a challenge.

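### The 80% power with 29 women per arm holds only if the outcome rates are 70% (control) and 34% (intervention), and the protocol supports neither rate

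*Protocol article*

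**What the plan says.** All references are to the protocol article.

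- **Statistical methods {14}** sizes the trial for a difference between two proportions: "the error rate of 5% with power = 80" per cent, a two-tailed alpha and equal arms.
- The control rate is "p2 = proportion of unexposed with the outcome: incidence in the control group: 70% (since no similar studies have been conducted locally". The same sentence then calls the 70% p1, although p1 is defined just above as the intervention rate.
- The intervention rate is 34%. Its source is two studies reporting "an improvement between 34 and 69% after delivering the interventions to pregnant women".
- The result is "The sample size needed for each group would be 29 pregnant women, and the total would be 58 participants".
- **Background and rationale {6a}** gives local figures before and during the pandemic: "perinatal depression increased by 10% (24% vs. 34.4%), and perinatal anxiety increased by 22.8% (16.4% vs. 39.2"%. It says these come from screening tools.
- **Eligibility criteria {10}** excludes women with psychiatric illness.
- **Outcomes {12}** makes the primary outcomes scores for depression, anxiety and COVID-19 phobia. **Statistical methods {20a}** analyses continuous outcomes with a linear mixed model that includes the baseline score, and binary outcomes with a logistic mixed model.
- **Discussion**: "face-to-face CBT revealed a protective effect (OR 0.64", 95% CI 0.53 to 0.75, and a preventive effect with OR 0.39, 95% CI 0.17 to 0.60.

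**The concern.** Both inputs to the power calculation look unsound. The control rate is put at 70% for want of local studies, yet the Background quotes local prevalences of about half that, and this trial screens out women with psychiatric illness. The intervention rate is a percentage improvement used as though it were the percentage of women who still have the outcome.

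The Discussion says the results will show whether the intervention is preventive and whether it belongs in the antenatal package. If the real power is far below 80%, a non-significant result cannot carry the negative half of that statement. A reader who trusts the 80% would give it too much weight.

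**Working it through.** **1. The plan's own figure.** Inputs: p1 = 0.34, p2 = 0.70, two-sided alpha 0.05 (z = 1.960), power 0.80 (z = 0.8416), ratio 1.

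- Printed (unpooled) formula: (1.960 + 0.8416)² × (0.34×0.66 + 0.70×0.30) / 0.36² = 7.849 × 0.4344 / 0.1296 = 26.3, so 27 per arm.
- Pooled-variance formula, mean rate 0.52: (1.960×√(2×0.52×0.48) + 0.8416×√0.4344)² / 0.1296 = (1.3848 + 0.5547)² / 0.1296 = 29.03. This is the stated 29; power at 29 per arm is 79.96%.

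So 29 reproduces from the stated inputs, though not by the printed formula.

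**2. The intervention rate.** A 34% relative reduction from 70% gives 0.70 × 0.66 = 46.2%, not 34%. The planned pair is an odds ratio of (0.34/0.66)/(0.70/0.30) = 0.22.

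**3. Power at 29 per arm for other rates.** Power = Φ{[|p1−p2|√29 − 1.960√(2p̄(1−p̄))] / √(p1(1−p1)+p2(1−p2))}. Example, 34.4% against 34.4% × 0.66 = 22.7%: (0.630 − 1.252)/0.633 = −0.98, so 16%. The last column uses the pooled formula in step 1.

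| Control | Effect | Intervention | Power at 29 | Per arm for 80% |
|---|---|---|---|---|
| 34.4% | 34% reduction | 22.7% | 16% | 233 |
| 34.4% | 69% reduction | 10.7% | 58% | 48 |
| 34.4% | OR 0.39 | 17.0% | 33% | 98 |
| 34.4% | OR 0.64 | 25.1% | 12% | 381 |
| 39.2% | 34% reduction | 25.9% | 19% | 193 |
| 39.2% | 69% reduction | 12.2% | 66% | 40 |
| 39.2% | OR 0.39 | 20.1% | 35% | 89 |
| 39.2% | OR 0.64 | 29.2% | 12% | 353 |
| 70% | 34% reduction | 46.2% | 45% | 67 |
| 70% | 69% reduction | 21.7% | 98% | 16 |
| 70% | OR 0.39 | 47.6% | 41% | 75 |
| 70% | OR 0.64 | 59.9% | 12% | 349 |

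For 80% power with 29 per arm, the intervention rate would have to fall to 5.6% (from 34.4%) or 8.5% (from 39.2%).

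**4. Loss to follow-up.** The calculation allows for none. With an assumed 20% loss, 29 × 0.8 = 23 per arm, and power at 34% against 70% is 70%.

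**5. The score outcomes.** An unadjusted two-sample t-test with 80% power detects a standardised difference d of 0.75 at 29 per arm and 0.84 at 23 per arm. Adjusting for baseline multiplies d by √(1−ρ²), where ρ is the correlation between baseline and follow-up. The protocol does not give ρ. At 29 per arm an assumed ρ of 0.5 gives 0.749 × 0.866 = 0.65, and 0.7 gives 0.749 × 0.714 = 0.53.

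**The case against.** The strongest reply is that the 70% may describe something other than the Background's figures. Those are separate prevalences of depression and anxiety, while the 70% is called an incidence of an outcome that is not named. The Objectives treat distress as depression, anxiety and COVID-19 phobia together, and no phobia rate is given. Depression or anxiety alone would reach 1 − 0.656 × 0.608 = 60% if independent and 34.4 + 39.2 = 73.6% if they never coincided. The remark about missing local studies may also mean intervention studies. This stands to the extent that a reader who infers a flat contradiction goes too far: the 70% is unexplained, not disproved. It does not rescue the calculation. No composite is defined, and anxiety is scored on a subscale of the depression instrument, so overlap is expected. Even at 70% the cited odds ratios give 41% and 12% power.

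Other stronger readings that the document does not support:

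- *The formula mismatch costs power.* It does not. The printed formula asks for 27, fewer than planned, and the pooled formula gives 29. This is a reporting error.
- *The planned effect lies outside the cited evidence.* An odds ratio of 0.22 is inside the 0.17 to 0.60 interval for the 0.39 estimate. It is outside 0.53 to 0.75 for the other.
- *Power is low for every effect.* A 69% reduction from 70% would have 98% power. But the calculation uses the 34% as a rate and does not argue for a 69% reduction.
- *The calculation fits no planned analysis.* Binary outcomes will be analysed. The fair point is that the primary outcomes are defined as scores.

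The Discussion does concede that the sample is small and that loss is possible. It ties sample size to generalisation, however, and leaves the 80% statement uncorrected. The loss figure used here is an assumption; loss by the third trimester, where the Abstract places the primary endpoint, could be lower than over the full year.

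**Conclusion.** The power statement is wrong as written. It is correct arithmetic for 70% against 34%, but neither rate is supported: the first is about twice the protocol's local prevalences without explanation, and the second is an improvement used as an incidence.

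With 29 per arm and the local prevalences as control rates, power is about 16% to 58% (34.4%) or 19% to 66% (39.2%) across relative reductions of 34% to 69%. That range assumes that the cited improvement is a relative reduction and that either prevalence stands in for the control rate. At the cited odds ratio point estimates power is 33% to 41% for 0.39 and about 12% for 0.64, over control rates from 34.4% to 70%. All figures use the pooled normal approximation, two-sided 0.05, with no loss unless stated. Neither the sample size nor the design has to change, only what is claimed for them.

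**What to change.** In Statistical methods {14}:

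1. Withdraw the unconditional 80% claim. State that it holds only for 70% against 34% with no loss, and name the binary outcome, its cut-off and its time point.
2. Justify the 70% or replace it. Replace the improvement figure with an intervention rate derived from it, stating whether the improvement is relative or absolute.
3. Report the power of 58 women at control rates of 34.4% and 39.2% over reductions of 34% to 69%, with and without a stated loss.
4. For the primary scores, give the detectable difference under the planned baseline-adjusted model with its assumed correlation. If d of 0.75 (29 per arm) or 0.84 (23 per arm) is quoted, label it as unadjusted.
5. As minor corrections that cost no power, print the pooled-variance formula that yields 29 and correct the label that calls the 70% p1.

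In the Discussion, state that a non-significant result will be interpreted from its confidence interval and not as showing that the intervention is not preventive.

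Cost: text only, with no extra women. The stated power becomes less favourable. The Trial status section says that recruitment has not begun, so the change can be made before any data exist.

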### Assignment of interventions

#### Sequence generation {16a}

Probability simple random selection will be selected randomly through the Automated Random Number Generator participants. The obstetric team on the delegation list will screen participants to identify those who fulfill inclusion criteria; then, they will be contacted through phone to consent; this step will continue until the calculated sample size is fulfilled. Each potential participant will be contacted a maximum of three times before withdrawing their name from the potential participant list.

The list of participants who consented to participate will be identified (codes only) with their phone number and contacted to arrange the teleconsultations sessions (six-video sessions) at their convenient time.

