#### Implementation {16c}

At the implementation level, another investigator will follow-up with the sessions. The investigator will also hand equal numbers of envelopes to each psychologist randomly. Each psychologist will then open the envelope and contact the patient to begin the teleconsultation session. Patients will give their consent verbally over the phone prior to any teleconsultation sessions.

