### Statistical methods

#### Statistical methods for primary and secondary outcomes {20a}

Quantitative variables will be described as mean and standard deviations, whereas the frequency with percentages will be calculated for categorical variables. Both the intervention group and control groups will be described in a table with all the characteristics. Chi-square test will be applied to compare percentages of categorical variables. Regression analysis will be carried to stratify data to eliminate potential confounders and effect modifiers. P value 0.05 (two-tailed) was considered for statically significant level.

We will analyze each continuous outcome with a linear mixed-effects regression model to account for the repeated measures over time. We will analyze binary outcomes with a logistic mixed-effects model. Mixed-effects models are the recommended statistical technique for analyzing clinical trials when outcomes are collected at repeated time points. This trial included outcome data at gestation weeks 14 to 40, 3 to 5 weeks postnatal, 2 to 4 months postpartum, 5 to 7 months, and 8 to 10 months postpartum or postnatal available for all participants who will be randomly assigned. The logistic mixed-effects model has the advantage of implicitly accounting for data missing at random. The estimated (adjusted) effect differences from these analyses therefore will be reported. The linear mixed-effects models will include the response variable, timepoint, randomized group, and baseline score as fixed effects. We will model an interaction between time and the randomized group as a fixed effect to estimate treatment effect at all timepoints. Gestational age and postpartum weeks will be included as covariates in the model. We will calculate standardized effect sizes with Cohen’s d.

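### The 80% power assumes 29 women per arm with observed outcomes, but the same 58 is the recruitment target and nothing is allowed for loss over about a year

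*Protocol article*

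**What the plan says.** Statistical methods {14} compares two proportions, 34% with the outcome under intervention and 70% under control, with 1:1 allocation, 80% power and a "standard normal deviate for the two-tailed test based on alpha level" of 0.05. It concludes: "The sample size needed for each group would be 29 pregnant women, and the total would be 58 participants". No term for loss appears. The Methods and analysis paragraph of the abstract targets the same 58. Under Sequence generation {16a}, women are screened and asked for consent by phone, and "this step will continue until the calculated sample size is fulfilled".

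On completeness of data the protocol says several things:
- Section {20a} describes outcome data from pregnancy through 8 to 10 months postpartum as "available for all participants who will be randomly assigned".
- Patient withdrawal lets a woman leave at any time.
- Section {20c} prepares for early, and possibly substantial or differential, discontinuation and for multiple imputation.
- The Discussion says that "loss of follow-up could be a challenge".
- Participant timeline {13} puts follow-up at about one year.

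**The concern.** The number needed for analysis and the number to be recruited are the same 58. The calculation treats every recruited woman as observed, while other sections foresee that some will not be. If women are lost, the trial has less power than it states for the comparison on which it was sized. The protocol intends its result to inform whether the service is recommended, so a null finding would be read against a power the trial may not have had. The mixed models and multiple imputation in {20a} and {20c} use partial data and address bias under their assumptions. They do not restore the 29 observed women per arm that the two-proportion calculation takes for granted.

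**Working it through.** **Inputs.** From Statistical methods {14}: p1 = 0.34, p2 = 0.70, difference 0.36, two-sided alpha 0.05 (z = 1.960), power 80% (z = 0.842), ratio 1. From {20a}: chi-square for categorical variables. No loss rate is given anywhere, so about 10%, 20% and 30%, equal in both arms, are assumed.

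**Reproducing 29 (pooled null variance, as in the chi-square test).** The mean proportion is (0.34 + 0.70)/2 = 0.52.

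- Null term: 1.960 × √(2 × 0.52 × 0.48) = 1.960 × 0.7065 = 1.385
- Alternative term: 0.842 × √(0.34 × 0.66 + 0.70 × 0.30) = 0.842 × 0.6591 = 0.555
- n = (1.385 + 0.555)² / 0.36² = 29.03 per arm

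This matches the stated 29 (strict rounding up would give 30). Power at 29 per arm is 79.96%, so there is no reserve.

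**The formula as printed (unpooled variance).** n = (1.960 + 0.842)² × 0.4344 / 0.1296 = 26.3, so 27 per arm. The printed formula does not yield 29. Taken at face value, it leaves a slack of two women per arm.

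**Power at smaller observed numbers.** With n observed per arm:

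- pooled: power = Φ[(0.36√n − 1.385) / 0.6591]
- unpooled: power = Φ[0.36√n / 0.6591 − 1.960]

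| Observed per arm | Lost of 29 | Pooled | Unpooled |
|---|---|---|---|
| 29 | 0 | 80.0% | 83.7% |
| 28 | 1 | 78.5% | 82.4% |
| 27 | 2 | 76.9% | 81.0% |
| 26 | 3 (3/29 = 10%) | 75.3% | 79.5% |
| 23 | 6 (6/29 = 21%) | 69.8% | 74.5% |
| 20 | 9 (9/29 = 31%) | 63.4% | 68.5% |

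Exact power of the uncorrected chi-square test at 29, 26, 23 and 20 per arm is 79.8%, 73.9%, 71.8% and 61.4%. That is the same picture, with the unevenness expected of a discrete test.

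**Which loss counts.** The abstract places the primary endpoint in the third trimester. For that endpoint only loss up to T1 matters. The Primary outcomes section extends the primary outcomes to 10 months postpartum, and there loss over the whole follow-up matters.

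**The case against.** **The printed formula leaves slack.** This stands in part. A reader might infer that any loss at all breaks the 80%. That is exact only for the pooled calculation. On the printed formula two losses per arm are tolerated, and the third takes power to 79.5%.

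**The protocol does not predict loss.** This stands. The Discussion says loss could be a challenge, {20c} is conditional, and no rate is given. Three-weekly calls, reminders and flexible booking are planned to limit it. A reader might infer that the protocol expects loss of a given size, but the text does not go that far.

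**The scores are analysed by a linear mixed model, not by comparing two proportions.** This stands as a limit on scope. As an illustration only, if a normal score were dichotomised to give 34% and 70%, the standardised difference would be about 0.94. A simple t-test would then have about 91%, 87% and 82% power at 26, 23 and 20 per arm. The table therefore does not show that the analysis of scores falls below 80%. The protocol's only power statement is nevertheless for proportions, and {20a} also plans binary analyses.

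**The sentence on complete data is loose wording.** This is plausible, since the same section refers to data missing at random. It still conflicts with {20c} and the Discussion, and costs nothing to correct.

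**Women who decline at the psychologist stage could be left out of the 58 and replaced.** A reader might infer this from Implementation {16c}, where "Patients will give their consent verbally over the phone prior to any teleconsultation sessions". The concealment and implementation sections place that contact after allocation, and the Participant timeline puts T0 after randomisation. Leaving such women out would be a post-randomisation exclusion, contrary to the intention-to-treat rule in {20c}.

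**Conclusion.** The point holds in a limited form. The sample size has no allowance for loss, and the figure needed for analysis is also the recruitment target, so the 80% is a best case. On the calculation that reproduces 29, the shortfall is about 5, 10 and 17 points at 26, 23 and 20 observed per arm. On the printed formula it is about 0.5, 5.5 and 11.5 points below 80%. These sizes rest on the protocol's own 34% and 70%, on assumed loss rates equal between arms, and on the two-proportion comparison. The documents do not support saying that the trial is underpowered for every planned analysis, or that a particular amount of loss is to be expected. How much loss bears on the primary comparison also depends on whether the third-trimester endpoint or the outcomes to 10 months are taken as primary.

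**What to change.** 1. In Statistical methods {14}, state that 80% power requires 29 women per arm observed at the analysed visit. Name the formula that produced 29, because the one printed gives 27.
2. In the same place, give an assumed loss rate with its basis and restate power at the resulting evaluable number. On the protocol's own rates, the pooled figures are about 75% at 26, 70% at 23 and 63% at 20 per arm.
3. In {20a}, replace the statement that outcome data are available for all randomised women with one that data will be sought from all of them at every visit.
4. Keep every randomised woman in the intention-to-treat set, including any who decline at the psychologist's contact after allocation.

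The cost is wording in two sections and a less favourable stated power. The target of 58 can stay. If the sponsor prefers to keep 80% despite loss, dividing 29 by one minus the loss rate and rounding up gives 33, 37 or 42 per arm (66, 74 or 84 in total) at 10%, 20% or 30%. The protocol reports that recruitment has not started, so either course is still open.
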